### Procedures

We will recruit 80 dyads (80 survivors and 80 caregivers) over the course of 12 months. Potential participants will be referred by the nursing team from unit rounds. The PI will give presentations to the nursing team to engage them as partners of the research and to make appropriate referrals for the study. Survivors who express interest in the study and their respective caregivers will meet either in person or virtually (phone or video call for COVID-19 safety efforts) with a CRC to learn more about the study and be screened for eligibility. Those who wish to participate will be given more information about the study as part of the consent and enrollment process. As mentioned earlier, dyads will be recruited within the first week of the survivor’s admission in the Neuro-ICU.

After determining eligibility study staff will meet with potential dyads to review the fact sheet for passive consent. After the document has been reviewed, study staff will answer any questions the participants may have. Participants will receive a description of all study procedures, information about potential risks and benefits of participation, and study contact information (including that of the IRB) in case questions arise at a later time. The fact sheet will also explicitly state that study participation is voluntary, and that participants may refuse to answer any questions that make them uncomfortable and may discontinue participation at any time. As consent is a continuous process, participants will be given a copy of the fact sheet and will be invited to ask questions about their participation at any point over the course of the study. In addition, participants will be assured that withdrawal from the study will not compromise their medical care in any way. Consent and authorization will be implied by voluntary completion of the survey (approved by the MGH IRB).

Survivors’ ability to enroll and participate will be determined based on nurses’ clinical judgments [28, 30]. For survivors unable to consent when first approached due to medical illness, we will enroll their informal caregiver and return for survivor enrollment later. Based on our previous prospective research in the Neuro-ICU, we expect the majority (~75%) of informal caregivers to be romantic/spousal partners of survivors. Only one informal caregiver will be enrolled for each survivor. If more than one informal caregiver is willing to participate, enrollment preference will be directed to the individual who is a) their spouse/partner b) the individual most responsible for their informal stroke aftercare, or c) the healthcare proxy.

Dyads will complete the initial study questionnaire in the privacy of the survivor’s hospital rooms, either using a researcher-provided iPad or their own preferred electronic device. At follow up timepoints (1 and 3 months) participants will either be emailed the link to the questionnaires or will complete the assessment over the phone with a CRC. Methods for both the baseline and follow-up data collection will be based on participant preference and ability. Dyads will have the option to complete the questionnaires in one 30-minute sittings, or over a series of meetings based on survivor related factors (e.g., fatigue, attention). The CRC for this study will assist participants with questionnaire completion as needed. We will collect clinical (e.g., relevant post-stroke complications) and demographic information from the electronic medical record throughout the study. Study procedures can be viewed in Fig 1.

### Data analysis

Preliminary analyses will be carried out to compare the relationship between psychosocial variables and demographics that will be included and/or controlled for in subsequent modeling. In aim 1, we will explore the trajectory of lifestyle factors and emotional distress from hospitalization through 3-month follow-up. Multilevel dyadic modeling (i.e., actor-partner interdependence model; APIM; See Fig 2 below) with distinguishable dyads will be used to determine influences of these factors onto each other over time and within the dyad [31, 51]. In the APIM for this study, the actor effect is the impact of a person’s lifestyle and emotional distress factors on his/her own lifestyle and emotional distress at 1 and 3 months. Similarly, their partner effect is the impact of a person’s factors on his/her partner’s same variables at 1 and 3 months. All dyad data will be restructured to a pairwise dyadic dataset. We will create grand mean centered scores that will be standardized using z-scores to obtain unstandardized and standardized regression coefficients for actor partner effects. The residual structure will be treated as heterogeneous compound symmetry in these APIM analyses [51]. In secondary analyses, we will stratify for relevant demographic (e.g., age, sex) and stroke type (e.g., subarachnoid hemorrhage [SAH], intracerebral hemorrhage [ICH]). We have successfully used these models and have published these results [23–25]. Fig 2 displays the APIM for the current study with measures and timepoints for HS dyads.

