## Abstract

Emotional distress (depression, anxiety, and PTS) and unhealthy lifestyle factors (e.g., smoking, alcohol consumption, poor diet, limited physical activity, medication adherence) are common in hemorrhagic stroke (HS) survivors and may increase risk for recurrence, morbidity, and mortality. Emotional distress and unhealthy lifestyle factors tend to be interdependent between survivors and their informal caregivers (e.g., family and friends who provide unpaid care; together called dyads), such that one partner’s lifestyle and coping behaviors influence the other’s behaviors, yet no research has closely examined this relationship in HS dyads over time. We will conduct a mixed methods study to quantitatively and qualitatively understand the longitudinal relationship between emotional distress and lifestyle factors across time in this population (HS dyads) to identify treatment targets to prevent emotional distress chronicity and stroke recurrence. In aim 1, we will assess emotional distress (i.e., depression, anxiety, and PTS) and lifestyle factors (smoking, alcohol consumption, poor diet, limited physical activity medication adherence/blood pressure control) in dyads of survivors of HS and their caregivers (N = 80), at three separate time points (hospitalization in the Neuro-ICU, 1, and 3 months later). We hypothesize that 1) lifestyle factors and emotional distress will be interrelated within and across time for both survivors and caregivers, and 2) lifestyle factors and emotional distress will be interdependent between survivors and caregivers. We also aim to explore the nuanced interplay between lifestyle factors and emotional distress and gain in depth information on barriers and facilitators for a dyadic intervention to optimize lifestyle behaviors and emotional functioning in HS dyads. Eligible patients will be adults who have a caregiver also willing to participate. Patients will be referred for study participation by the nursing team who will ensure that they are cognitively able to meaningfully participate. Multilevel dyadic modeling (i.e., actor-partner interdependence model; APIM) with distinguishable dyads will be used to determine influences of these factors onto each other over time. In Aim 2, we will conduct live video qualitative dyadic interviews (N = 20 or until theme saturation) at all time points from the same participants with and without emotional distress and at least one lifestyle risk factor, to understand the nuanced relationships between emotional distress and lifestyle behaviors, and barriers and facilitators to engagement in a skills-based psychosocial intervention. Interviews will be analyzed using inductive and deductive approaches. The present study is currently ongoing. So far, we enrolled 2 participants. Recruitment will end October 2022 with plans to analyze data by December 2022. The findings from this study will be used to further develop psychosocial interventions and inform novel treatments for survivors of HS and their informal caregivers.

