### Recruitment

Recruitment will occur at bedside in the Neuro-ICU at Massachusetts General Hospital (MGH). We will recruit participants through referrals from the nursing team of the Neuro-ICU at MGH from morning unit rounds. Survivors who express interest in the study and their respective caregivers will meet either in person or virtually (phone or video call for COVID-19 safety efforts if required) with a study research assistant to learn more about the study and be screened for eligibility. Those who wish to participate will be given information about the study as part of an informed consent process, as well as a resource sheet with the Principal Investigator’s (PI) contact information. These procedures (see Fig 1) will be completed in the survivor’s private hospital room. All dyads will be recruited within the first week of the survivor’s admission in the Neuro-ICU. We will recruit 80 dyads (80 survivors and 80 caregivers) over the course of 12 months. We have used this strategy successfully with previous studies within the Neuro-ICU and have had success with virtual data collection [28, 30, 32].

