**Fig 2 pone.0261635.g002:**
[figure not shown]
APIM design and study measures. Above describes the actor-partner interdependence model (APIM) and assessments used in our study. Multilevel dyadic modeling (i.e. APIM) with distinguishable dyads will be used to determine influences of lifestyle and emotional distress factors onto each other over time and within the dyad. We will administer lifestyle and emotional distress measures at each timepoint. In the context of this study, the actor effect is the impact of a person’s lifestyle and emotional distress factors on his/her own lifestyle and emotional distress at 1 and 3 months. Similarly, the partner effect is the impact of a person’s factors on his/her partner’s same variables at 1 and 3 months.

In Aim 2, we will conduct live video qualitative dyadic interviews (N = 20 or until saturation) at the same time points from participants (ICH and SAH stratified) with and without emotional distress and at least one lifestyle risk factor to understand the nuanced relationships between emotional distress and lifestyle behaviors, and barriers and facilitators to engagement in a skills-based psychosocial intervention. All qualitative data will be analyzed in NVivo 10 [52] using a hybrid inductive-deductive analytic strategy [53]. Similar to other methods we have used, we will de-identify and transcribe interviews verbatim and upload to NVivo 10. We will construct the primary codebook consistent with study goals. Transcript coders will practice coding a single transcript and we will modify the initial codebook based on usability. On future transcripts, coders will meet to reconcile any disagreements and discuss coding strategy.

Coders will start with deductive a priori themes consistent with study aims (i.e., relationship between lifestyle and emotional distress after HS) and will flexibly add new codes inductively to enhance the codebook. We will construct queries using the NVivo matrix function (i.e., crosstabs) to interpret and contextualize the qualitative data. This hybrid analytic approach will allow us to extract findings within Survivor and caregiver themes and will help us gain better understanding of the relationship between lifestyle and emotional distress after HS in survivors and informal caregivers and inform future interventions targeting these variables simultaneously.

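### The lagged APIM paths are to be read as impact and influence over time, but the text neither adjusts for the baseline outcome nor separates stable differences from change

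*Protocol article*

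**What the plan says.** In Data analysis, the protocol article says the multilevel actor-partner model "will be used to determine influences of these factors onto each other over time and within the dyad". It defines the two effects by their lag. For the actor, with follow-up counted in months: "the actor effect is the impact of a person’s lifestyle and emotional distress factors on his/her own lifestyle and emotional distress at 1 and 3". For the partner, on the same schedule: "their partner effect is the impact of a person’s factors on his/her partner’s same variables at 1 and 3 months". The Fig 2 legend repeats both definitions and again says the model is "used to determine influences of lifestyle and emotional distress factors onto each other over time and within the dyad".

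Two technical choices are fixed. On scores: "We will create grand mean centered scores that will be standardized using z-scores to obtain unstandardized and standardized regression coefficients for actor partner effects". On residuals: "The residual structure will be treated as heterogeneous compound symmetry in these APIM analyses". The section mentions demographic covariates and stratified secondary analyses. It does not mention the earlier value of the outcome, or a split between a person's usual level and departures from it.

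The hypotheses are milder than the analysis text. The Abstract expects that "lifestyle factors and emotional distress will be interrelated within and across time for both survivors and caregivers". That is a statement of association.

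**The concern.** Distress and lifestyle scores each contain a fairly stable part. Someone who is generally more distressed may generally have a poorer lifestyle, and partners may resemble each other. Baseline distress will then correlate with lifestyle at 3 months simply because both stable levels persist, even if neither ever moves the other. A lagged coefficient that omits baseline lifestyle largely carries that baseline correlation forward. Adding baseline lifestyle removes much of it but not all, because one reading is an imperfect measure of the stable level.

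This matters because the Abstract says the aim is to identify treatment targets, and Study design says the results will be used to develop a dyadic intervention. A target implies that changing one factor should move the other. Stable resemblance does not show that.

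**Working it through.** **Plan's own figure.** There is none to reproduce. The article gives no significance level, variance, stability or correlation.

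**Inputs from the article.** Sample size: "We will recruit 80 dyads (80 survivors and 80 caregivers) over the course of 12 months". Assessments at hospitalization, 1 month and 3 months.

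**Assumed inputs.** Two-sided 5% test; complete data; zero influence over time; share of score variance that is stable, λ = 0.5 to 0.8; stable correlation (distress with lifestyle, or between partners), r = 0.3 to 0.5; independent wave noise.

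**Step 1: does centring matter?** Subtracting one constant from every score cannot change a slope. A numerical check confirmed this: the four slopes were 0.125, 0.169, 0.133 and 0.040 both raw and grand-mean centred, with identical t-values. Centring neither creates nor removes the problem.

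**Step 2: closed form, own baseline distress to own 3-month lifestyle.** With no influence, the correlation of baseline distress with later lifestyle is λr, of baseline with later lifestyle λ, and of baseline distress with baseline lifestyle λr. Then:

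- Without baseline lifestyle: b = λr, SE = √[(1 − λ²r²)/78].
- With own baseline lifestyle: b = λr(1 − λ)/(1 − λ²r²), R² = (λ²r² + λ² − 2λ³r²)/(1 − λ²r²), SE = √[(1 − R²)/(77(1 − λ²r²))].
- With z = b/SE, rejection ≈ Φ(z − 1.96) + Φ(−z − 1.96).

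| λ | r | Without baseline: b / SE = z | Rejects | With baseline: b / SE = z | Rejects |
|---|---|---|---|---|---|
| 0.5 | 0.3 | 0.150 / 0.112 = 1.34 | 27% | 0.077 / 0.099 = 0.77 | 12% |
| 0.5 | 0.5 | 0.250 / 0.110 = 2.28 | 63% | 0.133 / 0.101 = 1.32 | 26% |
| 0.8 | 0.3 | 0.240 / 0.110 = 2.18 | 59% | 0.051 / 0.070 = 0.73 | 11% |
| 0.8 | 0.5 | 0.400 / 0.104 = 3.85 | 97% | 0.095 / 0.074 = 1.29 | 25% |

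The right-hand columns also apply to the same-variable partner path with own baseline in the model. Read r as the partners' stable correlation; the algebra is the same.

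**Step 3: simulation with both members' terms in the model.** In settings within the assumed ranges, with zero influence:

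| Path | Without baseline outcome | With baseline outcome |
|---|---|---|
| Own distress to own lifestyle | about 24% to 87% | about 10% to 19% |
| Partner distress to own lifestyle | about 6% to 13% | about 5% to 7% |
| Partner to own, same variable | not applicable | about 11% to 25% (own baseline in model) |

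These ranges depend on the settings chosen. Another set, with λ from 0.6 to 0.8, gave 31% to 95% and 10% to 28% for the own path, in line with the extreme corners in step 2.

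**Step 4: planned residual structure.** A further simulation used heterogeneous compound symmetry. Own paths without the prior outcome rejected 10% to 12% at λ = 0.3, r = 0.2, and 87% to 90% at λ = 0.7, r = 0.5. With the prior outcome and correlated traits they rejected 8% to 37%. When the distress and lifestyle traits were uncorrelated and the covariance unstructured, rates were nominal (4.4% to 5.9%), so the excess in the correlated cases comes from the correlated stable levels.

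**The case against.** **The article is a condensed account.** Exact model terms often sit in a fuller document, and the Fig 2 drawing is not available here. The actor definition, a person's lifestyle and distress on their own later lifestyle and distress, can be read to include the earlier value of the outcome. This stands in part: the article does not exclude baseline adjustment. But it does fix the interpretation, and even with baseline adjustment the residual confounding does not support impact or influence.

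**The hypotheses are about association.** This stands. A coefficient that blends stable differences with change can address whether factors are interrelated. The overreach is in Data analysis and the Fig 2 legend, which go further than the hypotheses.

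**Stronger readings that a reader might infer, and that the documents do not support:**

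- *Grand-mean centring is the fault.* It only moves the origin (step 1).
- *The model rejects its own null too often by some fixed multiple.* The model's null is no association. With correlated stable levels that null is false, so rejecting it is not a type I error; the error is in the reading. Any multiple rests wholly on assumed inputs.
- *The coefficient says nothing about influence.* It is a blend, so that is too absolute.
- *Influence should instead be read from each wave's deviation from the person's own mean.* That term has no time order. In simulation with no influence but shared wave-specific shocks correlated 0.2 to 0.3, it rejected 72% to 97%. Under a true lagged effect of +0.3 its mean estimate was −0.10, the wrong sign.

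**Conclusion.** The point holds as a mismatch between the analysis described and the words used for its results. As written, a significant lagged path need not reflect any influence over time. The exposure is large for own distress-to-lifestyle paths if the baseline outcome is left out, and moderate if it is included. Cross-variable partner paths are close to nominal after adjustment. Same-variable partner paths, which are the ones the article literally defines, stay above nominal even with own baseline in the model, because the partner's baseline is itself the predictor and nothing further is left to adjust for.

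All sizes rest on assumed stability and correlation and should be read as a range, not as a property of this study. If stable levels are uncorrelated the problem vanishes. The hypotheses as worded are not undermined.

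**What to change.** In Data analysis, state that every model of a 1- or 3-month outcome includes both members' baseline value of that same outcome. In the same section and in the Fig 2 legend, describe the resulting paths as prediction or association in place of impact and influence, since some stable-trait confounding remains after adjustment.

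A split into person mean and wave deviation may be reported as a sensitivity analysis, labelled as same-wave within-person association. Conclusions about influence over time should not rest on it. If it is used, the residual structure needs thought: with zero influence the deviation test rejected only about 0.6% to 4% under heterogeneous compound symmetry, against 4.9% to 5.9% with an unstructured covariance.

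Cost: no new data, since the baseline measures are already collected. Each model carries up to two more terms, and dyads without a baseline outcome need handling, so a little precision may be lost. In the closed-form cases above the standard error actually falls (for example 0.112 to 0.099 at λ = 0.5, r = 0.3), but the coefficient shrinks too, so fewer paths will be significant. The conclusion becomes more modest.

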**Fig 2 pone.0261635.g002:**
[figure not shown]
APIM design and study measures. Above describes the actor-partner interdependence model (APIM) and assessments used in our study. Multilevel dyadic modeling (i.e. APIM) with distinguishable dyads will be used to determine influences of lifestyle and emotional distress factors onto each other over time and within the dyad. We will administer lifestyle and emotional distress measures at each timepoint. In the context of this study, the actor effect is the impact of a person’s lifestyle and emotional distress factors on his/her own lifestyle and emotional distress at 1 and 3 months. Similarly, the partner effect is the impact of a person’s factors on his/her partner’s same variables at 1 and 3 months.

In Aim 2, we will conduct live video qualitative dyadic interviews (N = 20 or until saturation) at the same time points from participants (ICH and SAH stratified) with and without emotional distress and at least one lifestyle risk factor to understand the nuanced relationships between emotional distress and lifestyle behaviors, and barriers and facilitators to engagement in a skills-based psychosocial intervention. All qualitative data will be analyzed in NVivo 10 [52] using a hybrid inductive-deductive analytic strategy [53]. Similar to other methods we have used, we will de-identify and transcribe interviews verbatim and upload to NVivo 10. We will construct the primary codebook consistent with study goals. Transcript coders will practice coding a single transcript and we will modify the initial codebook based on usability. On future transcripts, coders will meet to reconcile any disagreements and discuss coding strategy.

Coders will start with deductive a priori themes consistent with study aims (i.e., relationship between lifestyle and emotional distress after HS) and will flexibly add new codes inductively to enhance the codebook. We will construct queries using the NVivo matrix function (i.e., crosstabs) to interpret and contextualize the qualitative data. This hybrid analytic approach will allow us to extract findings within Survivor and caregiver themes and will help us gain better understanding of the relationship between lifestyle and emotional distress after HS in survivors and informal caregivers and inform future interventions targeting these variables simultaneously.

### Data management

We will store data on encrypted and password secured computers to maximize confidentiality and security. Each subject will be assigned a unique and anonymous identifier that will be associated with all collected data including questionnaires and interviews. All paper files will be stored in a secure, locked location that is only accessible to the study team. All electronic questionnaire data will be stored on REDCap [33], a web-based, HIPAA-compliant data system available through MGH

All study staff have been trained in responsible research conduct through CITI training at MGH. The PI has trained the CRC on the importance of maintaining confidentiality and the utilization of ID numbers. Data will only be accessible only to trained study staff and will be kept under lock-and-key. Data will be identified by ID number only, and a link between names and ID numbers will be kept separately under lock and key.

